## Abstract

**Introduction:**

Very preterm infants (<32 weeks gestation) have an undeveloped primary endogenous circadian rhythm and are deprived abruptly of vital maternal circadian inputs after delivery. Postnatal care in neonatal intensive care units is characterised by constant levels of lighting and noise. Stress arising from disrupted cues for circadian rhythmicity likely disrupts development of coordinated circadian rhythms critical for neurogenesis, organ growth and development. We hypothesise that cycled environmental light and noise commenced soon after birth and continued until discharge home will improve cognitive outcomes compared with infants whose postnatal care comprises constant light (bright or dim) and constant noise.

**Methods and analysis:**

Australasian multicentre, two-arm, parallel-group, prospective, randomised, open, blinded-endpoint superiority trial in 868 infants born less than 32 weeks’ gestation. Infants are randomised to cycled environmental light and noise or routine care in a non-cycled hospital environment from soon after birth until discharge home. The intervention comprises wearing eye-masks and ear plugs from 20:00 to 6:00, followed by removal of these devices and exposure to normal environmental noise and 300-600 lux light from 6:00 to 20:00. The primary outcome is composite cognitive score on Bayley-4 developmental assessment at 2 years corrected postnatal age.

**Ethics and dissemination:**

The trial is approved by the Child and Adolescent Health Service Human Research Ethics Committee under the National Mutual Acceptance Scheme in Australia. Infants are randomised to intervention or control group after informed parental consent is obtained. Results of the CIRCA DIEM Study will be disseminated widely via presentations at local, national and international conferences, publication in international peer-reviewed journals and inclusion on the study website. Information about trial findings will also be communicated directly to the parents/guardians of trial participants through the regular study newsletter. The trial investigators will seek opportunities to communicate study results to the lay public through media and social media avenues.

**Trial registration number:**

ANZCTRN12618000371291.

STRENGTHS AND LIMITATIONS OF THIS STUDYThe study is powered to identify a 4-point increase in cognitive scale on the Bayley-4 assessment at 2 years corrected postnatal age.The study will use a rigorous statistical analysis using the Estimands Framework.The study protocol incorporates an integrated biobank and physiological substudies to facilitate future discovery research to explore mechanisms underlying clinical outcomes.While inability to blind the intervention is a study limitation, the trial steering committee, all outcome assessors and study statisticians are blinded to group assignment.

## Introduction

### Background and rationale

#### Burden of illness

 Preterm infants are at increased risk of chronic health problems including neurodevelopmental conditions, cerebral palsy, mental health, respiratory, renal, cardiovascular, metabolic, infectious and cancerous complications in later life,^1
2^ each of which is associated with chronodisruption.^3^

Cognitive impairment is the major and most distressing disability arising from preterm birth and the primary concern for parents and carers of preterm infants after hospital discharge. Premature babies also exhibit higher rates of adverse motor, behavioural and psychiatric outcomes in late childhood compared with children born at term gestation, even in the absence of recognised perinatal brain injury.^4^

#### Role of circadian rhythms in development

The vital role of an intact circadian rhythm for development of multiple body organs and systems is increasingly evident, and especially for the developing brain. The fetus is dependent on maternal circadian physiological (eg, temperature; melatonin and cortisol), auditory, tactile and kinaesthetic sensory cues to orchestrate developmental processes until near term.^5
6^ These maternal cues entrain the fetal circadian rhythms to the external light-dark cycle prior to development of endogenous fetal circadian rhythms.^7^

#### Effect of preterm birth on development of circadian rhythms in the premature newborn

Very preterm infants (<32 weeks gestation) have an undeveloped primary endogenous circadian rhythm^8^ and are deprived abruptly of vital maternal circadian inputs after delivery. Furthermore, very preterm infants are cared for in neonatal intensive care units (NICUs) characterised by constant levels of lighting and noise and are exposed to neuroactive medications (eg, caffeine, glucocorticoids) at non-physiological times. Stress arising from disrupted cues for circadian rhythmicity likely disrupts development of coordinated circadian rhythms critical for neurogenesis, organ growth and development,^9
10^ including disruption of white matter organisation,^11^ a critical determinant of cognitive function in childhood.^12^ The lack of an endogenous circadian rhythm for infants born preterm may also detract from the quality and quantity of sleep,^13^ which is critical to neurodevelopment.^14^ Disrupted circadian rhythms also reduce capacity for selective attention and executive function^15^ that are frequently impaired in survivors of preterm birth,^16
17^ and increase vulnerability to autism spectrum disorder. Importantly, circadian disruption also exerts key programming effects on the developing clock, increasing risk for later metabolic disease.^18
19^ Infants born very and extremely preterm are at highest risk of prolonged chronodisruption, due to the extended period of hospitalisation prior to discharge to a home environment.

#### Current recommendations about environmental conditions in the NICU

The American Academy of Pediatrics (AAP) suggested introducing regular cycles of day-night lighting in the NICU in 1997.^20^ However, there is no substantive clinical evidence to support this practice and few units achieve adequate (200 lux) separation of artificial night and day. To the contrary, the widely implemented Neonatal Individualised Developmental Care and Assessment Program recommends continuous dim lighting (<20 lux) for 24 hours/day during early postnatal life, to emulate the darkened environment of the uterus.^21^ However, this continuous dim lighting eliminates any environmental zeitgeber input to the suprachiasmatic nucleus (the ‘master clock’), which the fetus normally receives from circadian maternal cues. Importantly, even low levels of white light inhibit melatonin secretion, and in animal studies result in increased anxiety and delayed growth.^22^ The most recent Cochrane systematic review of cycled light in the intensive care unit for preterm or very low birth weight highlighted the need for a large, multicentre study with long-term follow-up. Most studies performed to date have evident or uncertain selection bias, and lack of clarity around outcome assessment (detection bias) and reporting bias, and involved single centres. The impact of cycled light for neurodevelopmental outcomes has not been considered. Importantly, preterm infants who are exposed to cycled light from birth develop circadian rhythmicity in melatonin profiles as early as 5 days of age.^23
24^ This observation indicates they can respond to cycled light and is consistent with the timing of functionality in the retinohypothalamic pathway.^25^

The AAP recommends that NICU noise levels should not exceed 45 dB,^18^ but this maximum exposure is rarely achieved with NICU noise levels often between 55 and 70 dB.^26^ There are no current recommendations about cycled noise in the NICU and it is unknown whether noise is a zeitgeber that entrains circadian rhythms. There are no studies of cycled noise exposure in preterm infants. However, one small (n=24) study evaluated the use of silicone earplugs worn throughout the admission in very low birth weight (<1500 g) infants within a single centre. A mean (95% CI) increase in weight at 34-week post-menstrual age (PMA) of 225 (45, 405) g was noted in the group assigned to earplugs compared with controls. Follow-up at 18–22 months was only completed for 12 infants, but reported mean (95% CI) increases in the Bayley Mental Developmental Index of 15.5 (3.0, 28.0) points and in head circumference of 2.6 (1.0, 4.2) cm for the six infants that wore the earplugs compared with the six infants in the control group.^27^ These promising outcomes need to be validated in an adequately powered trial with a primary neurodevelopmental outcome.

### Choice of comparators

Numerous environmental cues in hospital nurseries can delay development of endogenous rhythms, including light, noise, temperature regulation, feeding schedule and timing of neuroactive medications such as caffeine and steroids. Of these, light, noise and medication timing are likely the major disruptors of endogenous rhythms and are also most easily modified. The most recent Cochrane systematic review of cycled light for preterm infants acknowledged that the effect of a combination of interventions may be important for postnatal development of circadian rhythms in hospitalised preterm infants, rather than cycled light alone.^28^

#### Significance

Cycled environmental care is based on solid physiological principles and the increasing awareness that long-term well-being across multiple health domains is critically dependent on the integrity of circadian functions.^1^ It provides a simple, low-cost, attractive and pragmatic option for early postnatal development of endogenous circadian rhythms. The incorporation of these principles into the pragmatic design of the multicentre CIRCA DIEM trial will facilitate broad generalisability. A positive trial outcome would enable immediate adoption of cycled environmental care as routine neonatal management, with a potential to have lifelong health, welfare and socioeconomic benefits for the infants and their families.

### Objectives

#### Aim

To establish whether targeted individual diurnal cycling of environmental light and noise levels results in improved neurodevelopmental social, psychological, physiological and economic outcomes of infants born very preterm compared with more constant background lighting and noise environments.

#### Hypotheses

##### Primary hypothesis

Exposure to cycled light and noise from birth until discharge home will increase median cognitive score on the Bayley-4 at 2–3 years corrected postnatal age (cPNA) by 4 points compared with care in more constant background noise and lighting environments.^29^

##### Secondary hypotheses

Compared with more constant background noise and lighting environments, exposure to cycled light and noise from birth until discharge home will:

improve neurodevelopmental scores at 2 years cPNA;not increase mortality or neonatal morbidities;result in more rapid development of endogenous circadian rhythms;reduce parental depression and anxiety and improve parent–infant interactions anddecrease socioeconomic costs of premature birth.

## Methods

### Patient and public involvement

A consumer representative ([name]) and the Preterm Community Reference Group at The Kids Research Institute Australia will provide consumer and community input to the steering committee, trial design and trial materials including reporting of outcomes to incorporate patient and family perspectives.

### Trial design

The CIRCA DIEM is an Australasian multicentre (11 sites), two-arm, parallel-group, prospective, randomised, open, blinded-endpoint (PROBE) superiority trial undertaken in a broad group of infants at highest risk for prolonged chronodisruption (very and extremely preterm infants) with a primary neurodevelopmental outcome (cognition). The participant flow chart for the study is shown in figure 1.

**Figure 1 F1:**
[figure not shown]
CIRCA DIEM Study flow chart. ADOS-2, Autism Diagnostic Observation Schedule, Second Edition (Toddler Module); ASQ, Ages and Stages Questionnaire; CESD-R, Centre for Epidemiologic Studies Depression Scale–Revised; cPNA, corrected postnatal age; CSBC-ITC, Communication and Symbolic Behaviour Scales Infant-Toddler Checklist; EPDS, Edinburgh Postnatal Depression Scale; GAD-7, Generalised Anxiety Disorder Scale-7; GMA, General Movements Assessment; ITSEA, Infant Toddler Social Emotional Assessment; MPAS, Maternal Postnatal Attachment Scale.

### Study setting

The study will be undertaken in NICUs in major (tertiary) perinatal centres (primary recruiting sites) and supporting regional units (secondary sites) across Australia and New Zealand. The trial commenced on 4 February 2019. Last data collection is anticipated by 30 June 2029.

### Eligibility criteria

A register of potentially eligible infants will be documented by each study site to ensure transparent reporting of the study population.

#### Inclusion criteria (all must be satisfied)

born at <32 weeks PMA by best obstetric estimate (inborn or outborn).initial care is at a perinatal centre where routine care does not include formal environmental light/noise cycling.informed parental consent to trial participation, obtained either prior to or after birth (<168 hours for infants <28 weeks PMA, or <72 hours for infants ≥28 weeks PMA and <32 weeks PMA).

#### Exclusion criteria (any one or more mandates exclusion)

have a congenital neurodevelopmental abnormality or medical condition that would contraindicate the use of the interventional product(s)are critically ill and not expected to surviveunwilling or deemed unlikely to return for Bayley-4 follow-up at ~2 years cPNA; (eg, >200 km from tertiary centre and not enrolled in funded follow-up programme, itinerant family)anticipated discharge to a non-participating neonatal unit before 8 weeks postnatal age (for infants <28 weeks PMA).

### Intervention and comparator

Continuous light (either continuous bright light or continuous dim light/near darkness) is current standard of care in most NICUs. Continuous dim light generally targets 5–20 but, in some units, may include background lighting up to 100 lux. Cot covers typically remain in place 24 hours/day in the first weeks/months after birth. Eye masks are routinely only used for brief periods in association with phototherapy treatment, when they are worn 24 hours/day.

Most neonatal units do not routinely use ear protection for cycled day/night exposure to environmental noise, although earmuffs are occasionally applied for 24 hours/day for short periods when infants are receiving high-frequency ventilation.

#### Intervention description

##### Light

For the intervention group, the CIRCA DIEM Study will target cycled light from 0 lux at night to a range of 300-600 lux during daytime as this level was defined as safe for preterm infants.^26^ We thus anticipate a minimum separation of 200 lux between the intervention group and comparator group for daytime light exposure,^30^ and a 300 lux difference between daytime/night-time light intensity for the intervention group to ensure adequate light stimulus for entrainment of the endogenous circadian rhythm. The intervention will commence as soon as possible after randomisation and continue until discharge home or (for infants hospitalised for longer than 8 weeks) for a minimum of 8 weeks after commencement of the intervention.

Conversely, the CIRCA DIEM Study will use a pragmatic definition of non-cycled light environment for the comparator group as a difference between daytime and evening light intensity that does not exceed 100 lux.

##### Noise

There is no information on what difference in daytime/night-time noise might promote circadian rhythm entrainment in animal or human data. For the intervention group, we therefore use a pragmatic approach with application of ear plugs overnight to reduce background and peak noise exposure of approximately 22 dB. The application of these earplugs will reduce noise exposure overnight for most infants in the intervention group to levels that approach or minimally exceed the maximum exposure of 45 dB recommended by the AAP.^31^

Conversely, the comparator group will not receive any hearing protection unless prescribed 24 hours/day for short periods for clinical reasons (eg, receiving high-frequency ventilation).

##### Application of the study intervention

Ear plugs and eye masks will be applied in the evening at 20:00 and removed at 6:00 the following morning to provide a 10-hour intervention night period that still allowed parent–infant eye contact and sound for evening parental visits. Cot covers may also be used overnight. Eye masks can be removed for breast feeds but will otherwise stay in place overnight to minimise risk of inadvertent exposure to white light during procedures. Portable bedside lux metres are used to adjust bedside lighting to ensure 300-600 lux lighting exposure is achieved in the daytime.

### Criteria for discontinuing or modifying allocated interventions

The intervention may be discontinued prior to discharge home in participants randomised or allocated to the intervention group if they (1) received a minimum of 8 weeks of the intervention and are being discharged to a non-participating regional unit or (2) have reached term equivalent (40 weeks PMA) and are being transferred to another hospital ward for long-term care. Discontinuation of the intervention, or modifying the intervention (eg, avoiding light exposure during the day during periods of critical illness) outside these criteria will represent a protocol deviation, including discontinuation of the intervention due to an adverse event attributed to the trial intervention as assessed by the local site investigator. Attending physicians may withdraw a participant from the study if they develop a study related complication. Parent(s)/guardians may withdraw their infant from the study at any time. Parental/guardian permission to continue to collect infant data after study withdrawal will be sought.

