### Adverse events

Adverse events during the intervention period will be assessed from randomisation until death or discharge home from hospital, or 44 weeks PMA, whichever occurs soonest.

The 2016 recommendations of the National Health and Medical Research Council for safety reporting^43^ will be followed by the CIRCA DIEM trial.

Study related adverse events during the intervention period will include

ROP with a stage III or greater, or stage II with Plus disease on International Classification of Reinopathy of Prematurity Third Edition.Skin damage from use of wearables.Any perceived safety issue associated with the intervention devices.

Study related serious adverse events during the intervention period will include

Death before discharge home from hospital deemed potentially associated with the intervention.Any perceived life-threatening event during hospitalisation associated with the intervention devices.

Study-related serious adverse events occurring following the intervention period will include death after discharge and before 2 years of age associated with the intervention.

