##### Primary analysis

Standardised cognitive scores will be compared between the intervention and control group at 24 (20–36) months cPNA (primary outcome) using the Wilcoxon-Mann-Whitney test and summarised using the median of differences (Hodges-Lehmann estimator), with asymptotic 95% CI. The primary estimand will be detailed in the SAP, excluding non-randomised siblings from multiple births. In brief, missing primary outcome data due to death will be replaced with a score of 55 (corresponding to –3 SD), or with a score of 40 (–4 SD) in a sensitivity analysis. Missing data, including incomplete Bayley-4 scores, scores outside time window and those missing due to LTFU or withdrawal will be imputed (Amelia II R package) using prematurity strata and multiple birth as predictors.^46^ A separate estimand will be defined for the primary outcome excluding participants with all-cause missing data.

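### A physician may withdraw an infant from the study for a study-related complication, after which follow-up needs fresh parental permission, so loss of the 24-month score can depend on both arm and harm

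*Protocol article*

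**What the plan says.** The section on discontinuing or modifying allocated interventions holds two separate rules. Stopping or changing the devices outside the listed criteria is a protocol deviation, "including discontinuation of the intervention due to an adverse event attributed to the trial intervention as assessed by the local site investigator". The next sentence goes further: "Attending physicians may withdraw a participant from the study if they develop a study related complication". The section then adds: "Parental/guardian permission to continue to collect infant data after study withdrawal will be sought".

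The Adverse events section lists what counts as study related during the intervention period. The list includes "Skin damage from use of wearables", any perceived safety issue with the devices, and "ROP with a stage III or greater, or stage II with Plus disease".

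Under Primary analysis, scores outside the time window and "those missing due to LTFU or withdrawal will be imputed" with the Amelia II package. The named predictors are prematurity stratum and multiple birth. Deaths are scored 55, or 40 in a sensitivity analysis. A separate estimand leaves out participants with missing data. The Blinding section confirms that clinicians and parents know the allocation.

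**The concern.** A complication after randomisation is made a reason to leave the study, on the decision of a clinician who knows the allocation. The parents have already consented to the trial, and families thought unlikely to return for the Bayley-4 were excluded at entry. They must nevertheless agree a second time before data collection can go on.

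The trigger is not neutral between arms. Control infants wear no study devices, so device complications cannot occur in them. Severe ROP can occur in either arm, but whether it is judged related to the study depends on open-label attribution. If some of these infants lose their 24-month assessment, comparable control infants may stay in with their observed low scores while the intervention infants are replaced by typical imputed ones. That moves the primary comparison towards the intervention. Later harm in the withdrawn infants may also go unseen, and a later death receives the score of 55 only if the trial learns of it.

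**Working it through.** **1. The plan's own figures.** Inputs from the Sample size section: difference 4, SD 15, control score 85, 90% power, 312 per arm, 868 recruited, 10% loss to follow-up, 20% multiple births. Two-sided alpha of 0.05 is an assumption, since the article does not state it.
- Two-sample normal calculation: 296 per arm. Dividing by the Wilcoxon efficiency 3/π gives 310 per arm, against 312 stated.
- Inflation: 624 / (0.9 × 0.8) = 866.7, against 868 stated.
- Randomised infants per arm, leaving out non-randomised siblings: 434 × 0.8 = 347.

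The sample size reproduces and is not affected by this point.

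**2. What an affected infant is given.** Neither the complication, nor morbidity, nor the reason for withdrawal is among the named predictors. The imputed value is therefore a draw centred on the stratum mean. With no treatment effect, and on the protocol's assumption for controls, that is about 85.

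**3. Size of the shift.** Let w be the share of the intervention arm withdrawn and then lost, and g the number of points by which their true scores fall below the stratum mean. To first order,

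bias in the mean ≈ w × g.

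For example, 0.02 × 20 = 0.4. The Hodges-Lehmann estimate moves slightly less when g is large. It was simulated with scores N(85, 15), lost infants' true scores N(85 − g, 15), imputed draws from N(85, 15), and six runs of 3,000 per arm. Both w and g are assumptions; the article gives neither.

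| w (infants of 347) | g = 10 | g = 15 | g = 20 | g = 30 |
|---|---|---|---|---|
| 1% (about 3) | 0.10 | 0.12 | 0.14 | 0.24 |
| 2% (about 7) | 0.21 | 0.29 | 0.33 | 0.44 |
| 5% (about 17) | 0.49 | 0.69 | 0.88 | 1.17 |
| 10% (about 35) | 0.97 | 1.44 | 1.80 | 2.42 |

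Entries are points in favour of the intervention. As a share of the 4-point target, 0.1 is 2.5%, 0.44 is 11% and 1.17 is 29%. The 10% row uses up the whole loss-to-follow-up allowance on this one cause and is an outer bound.

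**4. Effect on the test.** This is the most asymmetric case: complications equally common in both arms, with the same deficit, but infants withdrawn and lost only in the intervention arm. There is no treatment effect, 347 per arm, a one-sided Mann-Whitney test at 0.025, one imputed draw per infant and 3,000 simulated trials. False superiority is 2.6% with no loss, 4.6% (g = 15) to 5.7% (g = 30) at w = 2%, and 7.3% to 16.0% at w = 5%.

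**5. Whether the other analyses correct it.** The estimand that excludes missing data drops the same infants, so the selection remains. The mixed-model secondary analysis adjusts for a count of neonatal morbidities, but its missing scores are filled in as for the primary estimand.

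**The case against.** The strongest reply is that a score is lost only if a physician withdraws the infant and the parents then decline or do not attend. Permission to continue will be sought, and parents who never asked to leave are likely to give it. This stands: a reader might infer that withdrawal automatically removes the 24-month score, and the text does not say so. It is why the low rows of the table are the more plausible ones.

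Second, the event most likely to go with poorer development, severe ROP, is not specific to one arm, while the clearly device-specific event, skin damage, has no documented link to the Bayley score. This also stands in part. A reader might infer that the rule can act only on intervention infants; the documents support only a possible imbalance through unblinded attribution. The Discussion itself names attrition bias from perceived differences in care, or from carers' lack of equipoise, as a limitation.

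Third, the article says that handling of missing data will follow the reason for missingness and be set out in the SAP, which is not shown. That could improve the imputation, but it cannot recover assessments that were never made.

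Three further inferences are not supported. Imputed infants stay in the analysis, so the rule does not contradict intention to treat or the statement that all randomised participants are included. Nothing shows that the deviation label on stopping devices steers clinicians towards study withdrawal. No passage reports that any physician withdrawal has occurred.

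**Conclusion.** The point holds in limited form. The protocol fixes a route by which primary-outcome and safety data can be lost in a way that depends on arm and harm, and the imputation it describes uses no information that would correct for this. The size is unknown because no withdrawal rate is given. Under the assumed deficits of 10 to 30 points, the bias towards the intervention is about 0.1 to 0.45 points if 1–2% of that arm is lost and about 0.5 to 1.2 points if 5% is lost, against the 4-point target. These figures assume that lost infants are imputed at the stratum mean and that no matching loss occurs among controls; loss in both arms would reduce them. If such withdrawals are very rare, or parents nearly always agree to continue, the effect is small. The case for acting is that the loss is avoidable and cheap to prevent.

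**What to change.** Change the data side only.
- State that a physician's decision under this sentence does not end follow-up. In-hospital outcomes, vital status and the 24-month Bayley-4 continue under the original consent unless a parent or guardian withdraws it.
- Give parents tiered options on the withdrawal form: stopping visits while allowing use of records and vital status, or full withdrawal.
- Offer the 24-month assessment to any family already withdrawn by a physician. The window runs to 36 months and primary outcome collection to early 2029, so this should still be possible for some.

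When the devices are stopped or modified is left to the sponsor.

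The cost is an amended sentence, a revised withdrawal form and a few more families to trace. The sponsor should confirm that the consent form, which is not shown here, already covers this follow-up.
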